## Abstract

**Background:**

Nonspecific low back pain (NSLBP) is a significant global public health concern that affects the health and well-being of individuals across different age groups, limiting their daily activities and reducing their quality of life. As Tuina (Chinese therapeutic massage) therapy and medicated oil are widely used in China, it is necessary to design a randomized clinical trial to assess the effectiveness of Tuina combined medicated oil (TNO) in treating NSLBP.

**Objective:**

This study aims to evaluate the efficacy and safety of Tuina therapy combined with medicated oil in treating NSLBP.

**Methods:**

One hundred participants will be enrolled and randomly allocated to either a TNO group (n=50) or a Tuina combined water group (n=50). Treatment will last for 4 weeks, with sessions 3 times a week, followed by a 4-week follow-up. The visual analog scale score is the primary outcome; secondary outcomes include the evaluation of treatment Japanese Orthopaedic Association scores, infrared thermography, muscle tension tests, and tenderness scores. All adverse reactions will be recorded.

**Results:**

The trial commenced in June 2023 and is expected to conclude in September 2025. In June 2025, key preliminary steps were completed, and the ethical review and clinical trial registration were concluded. Recruitment is proceeding as planned, with 100 participants enrolled to date. Data collection is underway, while formal data analysis has not yet commenced.

**Conclusions:**

The project’s purpose is to evaluate the effectiveness of TNO in alleviating pain and improving lumbar function in patients with NSLBP.

## Introduction

Nonspecific low back pain (NSLBP) clinical symptoms include low back pain, muscle tension, stiffness below the rib margin and above the gluteal sulcus, leg pain, numbness, and weakness. NSLBP is one of the leading causes of disability among workers in high-income and transitional countries, ranking sixth in overall disease burden [1,2]. NSLBP is a significant global public health issue that impacts individuals, their health, and society. It often recurs and imposes a burden on the economy. It is the most expensive medical condition in the United States, estimated at US $134.5 billion in 2016 [3,4].

According to an epidemiological survey [5], the incidence rate of NSLBP increased by 18% from 2006 to 2016. With the change of people’s lives and learning styles, low back pain is increasingly affecting younger individuals. A study of 404,206 adolescents from 28 countries found that 37% experienced low back pain every month or more often [6]. Risk factors associated with NSLBP include obesity, lack of exercise, poor occupational or lifestyle habits, depression, and other social and psychological factors [7]. Maintaining a normal weight, good physical health, proper posture, and regular exercise may reduce the risk, but evidence-based support is lacking [8,9].

NSLBP accounts for the highest proportion of low back pain [1]. NSLBP affects individuals of different age groups, limits their daily activity function, and reduces their quality of life [10,11]. There is no specific treatment for NSLBP; the purpose of therapy is to alleviate pain and its consequences, including any disabilities related to NSLBP. Traditional Chinese medicine (TCM) external treatment methods, Tuina, offer unique advantages in clinical applications, as they are noninvasive, have relatively low treatment costs, are simple to apply, and are highly acceptable [12-14]. Clinical studies on treating lower back pain with Tuina, both domestically and internationally, have demonstrated that massage therapy effectively reduces muscle and myofascial tension, promoting local metabolism [12,13,15,16].

Currently, the treatment methods for patients with NSLBP are divided into surgical and nonsurgical therapies. Nonsurgical therapies include cognitive behavioral therapy, exercise, manual therapy, physical therapy, acupuncture, and pharmacological therapy [17-20]. The North American Spine Society indicates that there is currently insufficient evidence to recommend or oppose a fusion surgery for lower back pain. There is also insufficient evidence to suggest that imaging results of lumbar fusion are associated with better clinical outcomes, with a level I recommendation [14]. Different treatment methods have their advantages and disadvantages. Surgical therapy has high costs, while traumatic treatment is insufficient, and its traumatic nature limits its effectiveness. Nonsurgical therapies, such as exercise therapy, can be challenging to adhere to. The practical and convenient treatment methods must be explored in clinical practice. Tuina acts on the body’s surface through mechanical stimulation as an alternative and complementary therapy. Patients easily accept Tuina therapy and feel highly comfortable. Medicated oil is an effective, safe, and easy-to-use treatment [21,22]. However, clinical trials of Tuina combined medicated oil (TNO) for treating lower back pain generally have a low level of evidence-based methods, lack a high-quality randomized controlled trial design, and are not included in clinical diagnosis and treatment guidelines.

Tuina has unique advantages as one of the traditional external treatment methods in TCM. Previous studies have confirmed its role in various waist-related diseases such as NSLBP, lumbar disc herniation, and acute lumbar sprain [23-26]. Tuina therapy emphasizes the balance of muscles and bones, prioritizing tendons and the presence of tendons that can lead to dislocation of bones, both of which are primary pathogenic factors. Tuina has a holistic view of TCM in the practice of “principles, methods, formulas, and techniques,” and has the characteristics of benign and bidirectional regulation in the treatment mechanism. It has been widely applied in clinical practice to treat musculoskeletal diseases.

The Flying Eagle Wood Lok Medicated Oil (FEMO) used in this study has effects that include warming meridians, dispelling cold, wind, and dampness, promoting blood circulation, and relieving pain. Medicated oil is a traditional Chinese patent medicine and a simple preparation made according to the principles of TCM. It exhibits characteristics of percutaneous penetration, rapid onset, and minimal gastrointestinal side effects.

The main components of FEMO consist of *Panax notoginseng* (Burk.) F.H. Chen, *Aconitum carmichaelii* Debx., *Arisaema erubescens* (Wall.) Schott, *Pinellia ternata* (Thunb.) Breit, *Carthamus tinctorius* L., methyl salicylate (wintergreen oil), menthol, camphor, eucalyptus oil, lavender oil, rose oil, and olive oil [27,28]. Modern medical research has shown that medicated oil has anti-inflammatory, analgesic, and preventive effects on pressure ulcers [29]. It is applied to treat muscle soreness, rheumatic bone pain, old and new sprains, arthritis pain, mosquito bites, sprain swelling and pain, low back and leg tendon pain, bone spurs, sciatica, and other diseases. NSLBP is one of its indications. For usage, follow the instructions and apply Tuina techniques, including finger pressure, for 15‐20 minutes to enhance the effectiveness of the drugs.

Although Tuina is widely used in the prevention and treatment of NSLBP, the current literature on its efficacy often lacks a rigorous experimental design, significantly weakening the persuasiveness of the research results. Although clinical trials have demonstrated effectiveness, no relevant evidence exists to explain the mechanism of action, which also applies to traditional Chinese patent medicines and simple preparations when rubbed with Tuina. This study is based on combining manual therapy with the external application of medicated oil in treating NSLBP, to fully leverage the complementary advantages of manual therapy combined with external treatment drugs. This study aims to provide an effective method for treating NSLBP and to objectively evaluate the clinical application of medicated oil by combining TCM Tuina with medicated oil.

## Methods

### Ethical Considerations

This study has been approved by the Ethics Committee of Shanghai Municipal Hospital of Traditional Chinese Medicine (2023SHL-KY-96-01). All participants provided written informed consent before participation. Participant privacy and confidentiality were strictly protected throughout this study; all data were anonymized and stored securely, and no personally identifiable information was disclosed. Participants received no compensation.

### Study Design

The research is a single-site study, parallel-controlled, randomized controlled trial. We will recruit 100 patients with NSLBP from the Shanghai Municipal Hospital of Traditional Chinese Medicine. Participants will receive informed consent during the recruitment process and will have equal opportunities to be randomly allocated to the TNO or Tuina combined water (TNW) groups. Due to limitations in intervention methods, outcome evaluators and statisticians will be kept blinded to the treatment assignment. Evaluators will evaluate and analyze the results at 5 time points (preintervention, 1, 2, and 4 wk after intervention, and 1-mo follow-up). Data management and statistical analysis will be performed at the Shanghai TCM Hospital Research Department. Figure 1 provides a visual representation of the research design, while Figure 2 displays the research schedule.

**Figure 1. F1:**
[figure not shown]
The trial flowchart. This study is a randomized controlled trial. A total of 100 patients will be randomly divided into 2 groups, the TNO group and the TNW group. Each group has the same number of patients, and the trial will include a 4-week treatment period. During the treatment process, patients in the TNO group received massage combined with medicated oil intervention, while patients in the TNW group received massage combined with water intervention. Two outcome evaluations will be conducted at 5 time points: baseline, the first week, the second week, the fourth week of treatment, and the eighth week of follow-up. JOA: Japanese Orthopaedic Association scores; TNO: Tuina combined medicated oil; TNW: Tuina combined water; VAS: visual analog scale.

**Figure 2. F2:**
[figure not shown]
This study’s schedule shows the time points (wk [W]) for enrollment and assessment.

### Sample Size Calculation

Based on the preliminary experimental research results, the sample size was estimated, and G*Power (version 3.1; Heinrich-Heine-Universität Düsseldorf) software was used to calculate the sample size for each group. The sample size was calculated to detect a between-group difference in the change in visual analog scale (VAS) score from baseline to week 4 (end of treatment), based on pilot posttreatment data. No power calculations were performed for week 8 outcomes, which are considered exploratory.

For grasp 1, the testing level was set at *α*=.05 and *β*=.95, and the required sample size was calculated to be 42 per group, considering a 10% dropout rate. According to 1:1 parallel grouping, VAS’s mean for the 2 pre-experimental groups was 3.57 (SD 1.35) in the TNO group and 2.61 (SD 1.39) in the TNW group. Using the above parameters, 50 patients with NSLBP should be included in each of the 2 groups, yielding a mean difference of 0.96 and a pooled SD of 1.37 (corresponding to a Cohen *d* effect size of 0.70), indicating a moderate-to-large treatment effect. The high statistical power was chosen to ensure robust internal validity, particularly given the modest, single-center study design and potential overestimation of the effect size from pilot data.

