To control multiplicity, a hierarchical testing strategy will be applied. The primary end point (change in VAS from baseline to wk 4) will be tested at a 2-sided α level of .05. Secondary outcomes (JOA score, tenderness score, muscle tension, and infrared thermography) will be tested sequentially only if the preceding end point reaches statistical significance, thereby controlling the family-wise error rate. Longitudinal group-by-time interactions across all postbaseline time points will be considered exploratory.

Clinically meaningful improvement will be evaluated using responder analyses in addition to continuous outcomes. A reduction of ≥2 points on the VAS and an improvement of ≥4 points on the JOA score will be defined a priori as the minimal clinically significant difference. The proportions of responders will be compared between groups using generalized estimating equations, with effect sizes reported as risk ratios and 95% CIs.

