#### Analysis of the Primary Outcome

The primary outcomes will be evaluated at baseline, intervention 1 week, 2 weeks, 4 weeks, and follow-up. We will conduct a sensitivity analysis on missing data (intention-to-treat analysis). The primary end point is the average change in the VAS scale from baseline to week 4 (primary end point) and week 8 (durability assessment). The baseline covariates include height, gender, age, cardiovascular history, and weight. The entire outcome scale will be measured at baseline. When the distribution is normal, nonpaired *t* tests are used to compare 2 groups, and 1-way ANOVA and repeated measures ANOVA are used to compare multiple groups. Sensitivity analysis using multiple input techniques (chain equation inputs) will be included to evaluate the impact of missing data on the main results. In addition, we will compare participants randomly assigned to the TNO and TNW groups, who received treatment considered to have high fidelity allocation. The percentage of missing data is 20%, and 5 input datasets will be used for analysis, which is the recommended minimum quantity. Before conducting any analysis, investigate any missing data patterns, identify the reasons for the missing data, and investigate the patterns to determine the validity of the hypothesis.

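### The sample size section states 95% power and gives both 42 and 50 per group; on its own inputs and the planned two-sided test, 50 per group has about 91% power after 10% dropout, and 42 does not reproduce

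*Protocol article*

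**What the plan says.** Four statements in the protocol article bear on this point.

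- **Error rates.** Under Sample Size Calculation, "the testing level was set at *α*=.05 and *β*=.95". Sidedness is not stated there.
- **Effect.** The pilot values are "3.57 (SD 1.35) in the TNO group and 2.61 (SD 1.39) in the TNW group", "yielding a mean difference of 0.96 and a pooled SD of 1.37 (corresponding to a Cohen *d* effect size of 0.70").
- **Size.** The section first says "the required sample size was calculated to be 42 per group, considering a 10% dropout rate". Then, from the same parameters, "50 patients with NSLBP should be included in each of the 2 groups". It adds a justification: "The high statistical power was chosen to ensure robust internal validity", in part because the pilot may have overestimated the effect.
- **Test.** Under Statistical Analysis, the primary end point (change in VAS from baseline to week 4) "will be tested at a 2-sided α level of .05".

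A separate sentence under Analysis of the Primary Outcome reads: "The percentage of missing data is 20%, and 5 input datasets will be used for analysis".

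**The concern.** One set of parameters cannot yield both 42 and 50 per group. Since 42 is already described as allowing for dropout, 50 cannot be explained as 42 inflated for dropout. A β of .95, read literally, would mean 5% power; the sentence about high power shows that a power of .95 was meant. Neither size delivers that power for the two-sided test fixed later in the article.

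The article uses the power figure as an argument, as a cushion against an optimistic pilot effect, and that cushion is smaller than stated. The testing sequence adds some weight to this, because no secondary outcome is formally tested if the primary test misses. As printed, a reader cannot replicate the calculation.

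**Working it through.** **Inputs** (Sample Size Calculation, except the sidedness, which comes from Statistical Analysis): means 3.57 and 2.61; SDs 1.35 and 1.39; 1:1 allocation; α = .05 two-sided; power .95; dropout 10%.

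**Step 1: effect size.** Pooled SD = √((1.35² + 1.39²)/2) = 1.370. d = (3.57 − 2.61)/1.370 = 0.96/1.370 = 0.7007. The article's 1.37 and 0.70 reproduce.

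**Step 2: formula.** For n evaluable per group, the two-sample t statistic has 2n − 2 degrees of freedom and noncentrality d√(n/2). Two-sided power is the probability that its absolute value exceeds the t critical value at 1 − .05/2. The one-sided version uses the upper tail at 1 − .05. The required n is the smallest that reaches the target. Dropout inflation is n/(1 − 0.10).

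**Step 3: can the stated sizes be reproduced at 95% power?**

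| Test | Evaluable per group | Randomised per group, 10% dropout |
|---|---|---|
| Two-sided .05 | 54 (d = 0.7007) to 55 (d = 0.70) | 54/0.9 = 60 to 55/0.9 = 61.1, so 62 |
| One-sided .05 | 45 | 45/0.9 = 50 |

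The planned 50 is matched exactly by the one-sided calculation and not by the two-sided one. The normal approximation gives the same picture: 53 to 54 evaluable two-sided, 45 one-sided.

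The figure 42 appears in neither row, before or after inflation. Inflating 42 gives 42/0.9 = 46.7, so 47, which is not 50 either.

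**Step 4: power of the sizes printed** (d = 0.7007).

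| Evaluable per group | Meaning | Two-sided | One-sided |
|---|---|---|---|
| 38 | 42 randomised less 10% (42 × 0.9 = 37.8) | 85.4% | 91.6% |
| 42 | 42 read as evaluable | 88.7% | 93.8% |
| 45 | 50 randomised less 10% | 90.8% | 95.1% |
| 50 | 50 randomised, no loss | 93.4% | 96.7% |

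On the two-sided test, 50 per group does not reach 95% even with complete data. At 45 evaluable the type II error is 100 − 90.8 = 9.2%, against the implied 5%.

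**Step 5: the 20% figure, as a scenario only.** If it meant that 20% of week 4 values were missing, 50 × 0.8 = 40 evaluable per group would give 87.2% two-sided power on the same basis.

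**The case against.** The strongest reply is that the primary analysis is not a t test. It is a mixed model on change from baseline. The article calls its sizing a simplified comparison and admits in the Discussion that longitudinal correlation was not built in. If 1.37 is the SD of a post-treatment score, power for change depends on the baseline to week 4 correlation r, which is not given. Assuming equal SDs at both visits, the SD of change is 1.37 × √(2(1 − r)). With 45 per group the two-sided power is then about 85% at r = 0.4, 91% at r = 0.5 and 96% at r = 0.6. A likelihood-based model also uses partial data from dropouts. This stands as a limit: 91% belongs to the stated calculation, and the power of the mixed model cannot be computed from the article. It does not rescue the stated calculation, which fails on its own terms.

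Three stronger readings are tempting, and the article does not support them.

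- **That the software was run one-sided.** The match 45/0.9 = 50 suggests it, but the article does not say so. The origin of 42 is likewise unknown.
- **That the plan expects 20% dropout and so contradicts its own 10%.** The 20% stands in an unclear sentence about how many imputed datasets to use. Missing values across five visits and loss of participants are different quantities. The sentence needs clarifying, but it is not a clear contradiction.
- **That the trial is underpowered or its validity is undermined.** About 91% is still high, and the article also relies on assessor blinding, training and objective measures.

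**Conclusion.** The point holds as an error in the reported calculation. Power is labelled as β, two incompatible sizes come from one set of inputs, and the stated 95% is not delivered by either size under the two-sided test. The shortfall is about 4 percentage points with 10% dropout (90.8%) and about 1.6 with no loss (93.4%). Reaching 95% would have needed 60 to 62 randomised per group instead of 50.

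These figures assume that power of .95 was intended, that d is 0.70, and that the basis is the simple two-group t test the article describes. They do not give the power of the mixed model. The 87% figure is conditional on one reading of the 20% and is not part of the core finding.

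**What to change.** In Sample Size Calculation:

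1. Replace the β value with power = .95 as the intended target.
2. State from the calculation record which sidedness and which dropout inflation rule were used.
3. Remove 42 per group, or explain what it refers to.
4. Add a sentence labelled as recomputed, for example: *On the simplified two-group t-test basis, 50 randomised per group (45 evaluable after 10% dropout) gives about 91% power at two-sided α = .05 for a 0.96-point difference with SD 1.37.*

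In Analysis of the Primary Outcome, say what the 20% refers to. If it means missing week 4 values, add that power on the same basis would be about 87%.

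Do not enrol more patients. The article reports 100 enrolled and formal analysis not yet begun, so the correction can be made before results are known. The cost is wording only, plus a slightly less favourable power figure. The test, the estimand and the design do not change.

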### Participants Recruitment

This study used a randomized controlled, single-blind trial method, with participants recruited from the outpatient departments of Shanghai Municipal Hospital of TCM. A total of 100 patients were randomly assigned to an observation group (TNO) and a control group (TNM), with 50 patients in each group (Textbox 1).

Textbox 1.Inclusion and exclusion criteria.Inclusion criteriaMeeting the diagnostic criteria for the nonspecific low back pain set by the North American Spine Society and Chinese expert consensus [30,31].Being between the ages of 20 and 59 years.During the trial period of the research method, immediately stopping any therapies that may affect the determination of research effectiveness.Participating in this study, cooperating with the doctor’s arrangements, and signing an informed consent form.Exclusion criteriaExcluding specific low back pain lesions such as lumbar disc herniation and lumbar spondylolisthesis, and those related to bone joints and the spinal canal.Being patients with severe heart, lung, liver, and kidney diseases.Being individuals undergoing other clinical trials.Being individuals with a history of spinal surgery, spinal injury or deformity, or fracture.Being patients with combined acute infections, cancer, rheumatic and immune diseases, and mental illnesses.Being individuals with other primary functional disorders.

### Dropout Criteria

The exclusion criteria were (1) not persisting in treatment or not following the treatment plan, (2) voluntarily requesting withdrawal, (3) having other serious concurrent diseases during the treatment process, and (4) using other treatment methods in combination.

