#### Statistical Analysis

Although the sample size calculation was based on a simplified between-group comparison at the primary postintervention time point (wk 4), the primary outcome analysis will use a longitudinal modeling framework to account for repeated measurements appropriately. A linear mixed-effects model will be used, including fixed effects for treatment group, time, and group-by-time interaction, with a random intercept specified for each participant. An unstructured covariance matrix will be prespecified to model within-subject correlations across repeated VAS measurements (baseline, and wk 1, 2, 4, and 8). Sensitivity analyses using alternative covariance structures, including first-order autoregressive and compound symmetry matrices, will be conducted to assess the robustness of the results. The data analysis was performed using SPSS (version 27.0) statistical software, and the testing criteria were as follows: *α*=.05, with *P*<.05 considered statistically significant.

Given the longitudinal design with repeated measurements collected at 5 time points (baseline, and wk 1, 2, 4, and 8), all primary and secondary continuous outcomes will be analyzed rather than with independent *t* tests or simple ANOVA, which accounts for within-subject correlation and avoids violations of the independence and sphericity assumptions inherent in traditional methods.

In each linear mixed-effects model, fixed effects will include treatment group (TNO vs TNW), time (modeled as a categorical variable), and the group-by-time interaction, with a random intercept specified for each participant. An unstructured covariance matrix will be prespecified for the repeated measures, with sensitivity analyses using alternative covariance structures (autoregressive and compound symmetry) to assess robustness. The primary estimand is the between-group difference in change from baseline to week 4 (end of treatment), which is defined a priori as the primary time point based on the sample size calculation.

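### Post-randomisation exclusions, with intention-to-treat mentioned only as a sensitivity analysis, leave the primary week 4 comparison open to outcome-related omission of patients

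*Protocol article*

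**What the plan says.** Under Dropout Criteria, the Protocol article states: "The exclusion criteria were (1) not persisting in treatment or not following the treatment plan, (2) voluntarily requesting withdrawal". The list continues with "having other serious concurrent diseases during the treatment process, and (4) using other treatment methods in combination". True eligibility criteria stand separately in Textbox 1 (Participants Recruitment), so this second list concerns patients already in the trial.

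The only mention of intention-to-treat is under Analysis of the Primary Outcome: "We will conduct a sensitivity analysis on missing data (intention-to-treat analysis". The same paragraph makes chained-equation imputation a sensitivity analysis too ("Sensitivity analysis using multiple input techniques (chain equation inputs) will be included to evaluate the impact of missing data on the main results") and adds an adherence-restricted comparison: "In addition, we will compare participants randomly assigned to the TNO and TNW groups, who received treatment considered to have high fidelity allocation".

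Statistical Analysis specifies a linear mixed model over baseline and weeks 1, 2, 4 and 8, and an estimand: "The primary estimand is the between-group difference in change from baseline to week 4 (end of treatment". It attaches no population to that estimand and does not say how non-adherence or other treatment enters it. No sentence in the article says that all randomised patients are analysed in their assigned arm in the primary comparison.

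**The concern.** The primary endpoint is patient-reported pain. A patient who stops attending, or who turns to another treatment, may well do so because the pain has not improved. Omitting such patients takes out poor responders, and what remains is no longer a comparison of the groups formed by randomisation.

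The harm depends on removal differing by arm, and the article gives reasons why it might. Safety Evaluation says that the oil has warming or irritant ingredients, whereas the control is water. The Discussion concedes that some unblinding of participants or therapists cannot be ruled out. Washout Period and Concomitant Treatments required no washout and asked patients to stop other therapies at once, so returning to them is a realistic event.

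The planned checks would not show the problem. Standard chained-equation imputation assumes missing at random, as the mixed model does, and the high-fidelity comparison narrows the set further.

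**Working it through.** **Texts side by side.** Not persisting with treatment and concurrent disease during treatment can only occur after allocation. Use of other treatment mirrors the during-trial restriction in Washout Period and Concomitant Treatments. The word used for these events is exclusion. The only analysis tied to intention-to-treat is a sensitivity analysis, and the primary model has no named population. Nothing in the text stops an analyst from leaving these patients out of the primary comparison.

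**Inputs from the article** (Sample Size Calculation): pilot means 3.57 and 2.61, SDs 1.35 and 1.39, 50 per group. These reproduce the planning figures:

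- difference = 3.57 − 2.61 = 0.96
- pooled SD = √[(1.35² + 1.39²)/2] = 1.37
- d = 0.96/1.37 = 0.70

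**Inputs assumed**, because the article gives none: the share e removed in each arm; the correlation ρ between a patient's outcome and removal; no true effect; and removal of the whole patient.

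**Formula.** If the worst fraction e is removed on a normal variable correlated ρ with the outcome, the mean of those left shifts in the favourable direction by ρ × SD × φ(z_e)/(1 − e). Here z_e is the normal quantile at e and φ the normal density. The bias is the difference between the two arms' shifts.

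Values of φ(z_e)/(1 − e):

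- 5%: 0.1031/0.95 = 0.109
- 10%: 0.1755/0.90 = 0.195
- 15%: 0.2332/0.85 = 0.274
- 20%: 0.2800/0.80 = 0.350

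Bias for 5% vs 15%: ρ × 1.37 × (0.2743 − 0.1086) = ρ × 0.227. Bias for 10% vs 20%: ρ × 1.37 × (0.350 − 0.195) = ρ × 0.212.

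Type I error comes from simulation at 50 per arm (6,000 trials per setting, each imbalance run in both directions):

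| Removed | ρ | Bias (VAS points) | Type I error |
|---|---|---|---|
| 10% vs 10% | 0.3–0.7 | 0 | about 0.05 |
| 5% vs 15% | 0.3 | 0.068 | 0.057–0.060 |
| 5% vs 15% | 0.5 | 0.114 | 0.060–0.067 |
| 5% vs 15% | 0.7 | 0.159 | 0.088–0.091 |
| 10% vs 20% | 0.3 | 0.064 | 0.053–0.058 |
| 10% vs 20% | 0.5 | 0.106 | 0.065–0.069 |
| 10% vs 20% | 0.7 | 0.149 | 0.083–0.088 |

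Relative to the planned difference: 0.064/0.96 = 7% and 0.159/0.96 = 17%. With ρ = 0 there is no bias. The arm that loses more patients is flattered, so the bias can run either way.

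**If earlier VAS values stay in the model.** Take a harsher case: 2 vs 8 of 50 lost, with removal driven by outcome plus noise of equal variance. Deleting whole patients on the week 4 value gives a bias of about 0.19. Keeping their baseline, week 1 and week 2 values in the mixed model (assumed within-patient correlation 0.5 to 0.7) lowers this to about 0.1. If removal instead follows week 2 pain, the bias falls below 0.01.

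**The case against.** The strongest reply is that Dropout Criteria never says what exclusion means. It could be leaving treatment, leaving follow-up or leaving the analysis. The high-fidelity comparison is offered as an addition, which makes little sense if the main analysis already drops non-adherers. The intention-to-treat parenthesis could also describe how missing data are handled under that principle rather than demote it. All of this stands, and it is why omission from the primary analysis is a natural reading and not an established fact. It does not remove the point, because no sentence settles the matter and the words actually used point towards exclusion. Nor is this a detail merely left to an analysis plan: the article itself fixes both the exclusions and the role of intention-to-treat.

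Three stronger readings are tempting and not supported.

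- A reader might infer that the plan states these patients are removed from the primary comparison. It does not.
- A reader might infer that the type I error rises to 12% or 20%. Those figures need a correlation of about 0.71, losses of 2 vs 8 or 2 vs 12 out of 50, and deletion of whole patients. The documents support none of these, and the mixed model uses earlier values where they are kept.
- A reader might infer that the small number of imputations ("The percentage of missing data is 20%, and 5 input datasets will be used for analysis") makes the primary p value unstable. Imputation here is only a sensitivity analysis, so it cannot move the primary p value.

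**Conclusion.** The point holds as a conflict that must be reconciled. Post-randomisation events are called exclusion criteria, intention-to-treat is mentioned only as a sensitivity analysis, and the primary analysis set is not named. Followed as written, the plan can yield an analysis set that depends on the outcome.

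The illustrative size is moderate: about 0.06 to 0.16 VAS points and a type I error of about 5% to 9%. It rests on an assumed 10-point imbalance, an assumed correlation of 0.3 to 0.7 and removal of whole patients. The true size cannot be derived from the documents and could be nil. That the wording leaves the population open is certain. That the trial's result will be biased is not.

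**What to change.** Before unblinding:

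1. Reconcile Dropout Criteria with Analysis of the Primary Outcome by stating that the listed criteria do not remove patients from the analysis.
2. State that the primary mixed model includes all randomised patients in their assigned arm with all observed VAS data, including values recorded after non-adherence or other treatment.
3. Keep collecting VAS at weeks 4 and 8 for any patients still in follow-up who agree.
4. Label the high-fidelity comparison as supportive.
5. Add a delta-adjusted analysis by arm, so that at least one sensitivity analysis departs from missing at random.

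No clinical rule needs to change, and the list should not be recast as rules for stopping treatment, which the article does not state.

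The cost is wording and some programming. The Results section reports that formal analysis had not begun as of June 2025. There are two downsides. The estimate may be somewhat smaller than in adherers alone. And with 100 patients already enrolled by then, data cannot be recovered for those who have already left, so the sensitivity analysis has to carry that part.
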